## Abstract

Background: Early childhood educators (ECEs) influence young children’s early uptake of positive health behaviours in childcare settings and serve as important daytime role models. As such, it is imperative that post-secondary early childhood education programs provide students with the foundational knowledge and professional training required to confidently facilitate quality active play opportunities for young children. The primary objective of the *Training pre-service EArly CHildhood educators in physical activity (TEACH) study* is to develop and implement an e-Learning course in physical activity and sedentary behaviour to facilitate improvements in: pre-service ECEs’ self-efficacy and knowledge to lead physical activity and outdoor play opportunities and minimize sedentary behaviours in childcare. This study will also explore pre-service ECEs’ behavioural intention and perceived control to promote physical activity and outdoor play, and minimize sedentary behaviour in childcare, and the implementation of the e-Learning course. Methods/Design: A mixed-methods quasi-experimental design with three data collection time points (baseline, post-course completion, 3-month follow-up) will be employed to test the e-Learning course in early childhood education programs (*n* = 18; 9 experimental, 9 comparison) across Canada. Pre-service ECEs enrolled in colleges/universities assigned to the experimental group will be required to complete a 4-module e-Learning course, while programs in the comparison group will maintain their typical curriculum. Pre-service ECEs’ self-efficacy, knowledge, as well as behavioural intention and perceived behavioural control will be assessed via online surveys and module completion rates will be documented using website metrics. Group differences across timepoints will be assessed using linear mixed effects modelling and common themes will be identified through thematic analysis. Discussion: The TEACH study represents a novel, evidence-informed approach to address the existing gap in physical activity and sedentary behaviour-related education in Canadian post-secondary early childhood education programs. Moreover, e-Learning platforms, can be employed as an innovative, standardized, and scalable way to provide ECEs with consistent training across jurisdictions.

## 1. Background

Physical activity is a critical behaviour which supports young children’s (<5 years) physical, psychological, and academic development [1], while also enriching their lives in the here and now [2]. Despite its recognized benefits, physical activity levels have been noted to be varied, yet often low, in childcare centres [3]. For example, in one Canadian study, young children were reported to engage in only 1.54 min/h of moderate-to-vigorous physical activity (MVPA) while attending childcare [4]. Equally concerning, young children in childcare participate in high rates (~41 min/h) of sedentary time [5], which is associated with gains in adiposity and delayed cognitive development [6]. These compositional behaviours are worrisome as physical activity levels decline as children age [7], and, because attendance in childcare centres in Canada is high [8]; therefore, establishing health behaviours early in life is critical. 

In Canada, two-thirds of young children attend childcare [8], equating to almost 720,000 childcare spaces in centre-based facilities across the country, and over 280,000 children are enrolled in regulated home-based facilities. Further, children are spending, on average, 28 h per week in these settings [9]. With evidence showing that the childcare setting influences children’s physical activity behaviours [4], and the high reach and daily contact time with young children, the childcare environment is a prime setting through which to target the early years population.

For young children attending childcare, early childhood educators (ECEs) serve as their primary daytime role models; they are responsible for scheduling physical activity within their daily programming, while also facilitating active play. Therefore, these individuals have the potential to influence young children’s developmental experiences and day-to-day well-being [10]. With respect to daily programming, ECEs have a responsibility to support and engage young children in meaningful learning opportunities [11], such as physical activity, which nurture children’s holistic development and well-being [1,12,13]. Notwithstanding the benefits of physical activity during early childhood [1], opportunities for physical activity in childcare remain infrequent and undervalued [4,14,15,16].

Of particular concern, ECEs have communicated that they lack the self-efficacy needed to confidently facilitate physical activity for young children in childcare [17,18] and have acknowledged that this is primarily due to their limited professional training in physical activity domains, both during post-secondary education [19,20] and on-the-job [21,22]. A recent investigation of the physical activity knowledge, training, and self-efficacy among pre-service ECEs (*n* = 1292) enrolled at 61 Canadian colleges/universities revealed that only ~30% reported receiving physical activity and screen-viewing-specific training in their program and a mere 15% were familiar with national movement guidelines for young children [19]. More positively, pre-service ECEs who reported undertaking physical activity education demonstrated greater self-efficacy to engage young children in appropriate physical activity opportunities [19]. According to Bandura’s Social Cognitive Theory [23], self-efficacy is one of the most important and robust determinants of behaviour. In support of this theory, a recent meta-analysis revealed that task self-efficacy was the strongest psychological predictor of teaching performance [24]. As such, to effectively prepare pre-service ECEs for their work post-graduation, it is critical that their pre-service education scaffolds their development of self-efficacy in relation to a wide range of teaching contexts, including facilitating physical activity and children’s development of physical literacy.

Required learning outcomes for early childhood education programs delineate that graduates must be able to “promote regular, healthy physical activity in all children” [25]; however, the reported gap in pre-service ECEs’ physical activity-related knowledge and education [19] makes it apparent that they may not be provided with adequate educational experiences to match these expectations. Further, sedentary behaviour-related education is largely overlooked in post-secondary early childhood education curricula [19]. Without proper education, it is unlikely that pre-service ECEs will include appropriate and engaging physical activity and motor skill experiences into their daily programming and schedules, and actively plan to minimize sedentary opportunities, once they enter into the childcare profession [10]. Intervention research within post-secondary early childhood education programs is needed to understand how introducing a tailored physical activity and sedentary behaviour curriculum for pre-service ECEs influences their physical activity and sedentary behaviour-related self-efficacy, knowledge, and intentions, and thus, better prepares them for supporting and facilitating more active behaviours among young children in childcare.

Physical activity interventions which include professional development/training show promise for supporting improved physical activity levels among young children. For example, Pate et al.’s intervention, which trained childcare teachers in structured and unstructured physical activity opportunities and integrating physical activity into lesson plans, resulted in improved physical activity levels among preschoolers [26]. A different study by Ward and colleagues found online training for ECEs to be effective at improving educators’ physical activity practices in childcare [27]. Moreover, these authors noted the ease with which online training could be integrated into ECEs’ training and the reach online training could have for this field. Finally, Bai and colleagues reported an increase in ECEs’ self-efficacy to engage children to be active in nature play following a professional development program [28]. Collectively, training for ECEs shows potential for improving physical activity opportunities in childcare settings. Despite this, few interventions have explored the impact of professional learning uniquely (it is frequently provided in combination with physical activity programming) and little is known about the impact of this training in pre-service programs (i.e., during ECEs’ post-secondary training).

### 1.1. Study Rationale

The need to support pre-service ECEs’ self-efficacy and knowledge related to promoting physically active behaviours among young children in childcare is clear. Supplementary professional learning opportunities related to children’s physical activity, movement skill development, and appropriate sedentary behaviours, is likely to increase their confidence and ability to facilitate supportive physical activity environments, policies, programming, and practices in the childcare setting [19]. The traditional in-person approach to professional learning for ECEs, while effective [29], is resource-intensive, and thus, lacks feasibility for large-scale implementation. Building on the success of past training for ECEs [29], this study will adopt an innovative approach by using an e-Learning platform to deliver tailored education to pre-service ECEs at the post-secondary level, addressing a critical gap in Canadian early childhood education curricula. The product will include an evidence-informed, easily accessed physical activity and sedentary behaviour course which can be integrated into early childhood education programs across Canada and adapted for use in global contexts.

### 1.2. Study Objective

The primary objectives of the Training pre-service EArly CHildhood educators in physical activity (TEACH) study are to examine if the e-Learning course increases pre-service ECEs’: 1. self-efficacy to engage children in physical activity and outdoor play, and minimize sedentary behaviour in childcare; and, 2. physical activity and sedentary behaviour-related knowledge. The secondary objectives of the study are to explore: 1. pre-service ECEs’ behavioural intention and perceived behavioural control to promote physical activity and outdoor play and minimize sedentary behaviour in childcare; and, 2. implementation (e.g., fidelity, feasibility, acceptability, pre-service ECEs’ and early childhood education program instructors’ experiences) and potential scalability (via the Consolidated Framework for Implementation Research (CFIR) checklist) of the e-Learning course. 

## 2. Methods

### 2.1. Study Design

A mixed-methods quasi-experiential design will be employed to test the effectiveness of the TEACH e-Learning course at improving pre-service ECEs’ physical activity and sedentary behaviour-related self-efficacy and knowledge. Purposefully selected English-speaking colleges/universities offering an early childhood education program in Canada (i.e., clusters) will be randomly assigned to the experimental (*n* = 9) or comparison (*n* = 9) condition. A 4-module e-Learning course (hosted on a secure learning management system platform) will be implemented by schools assigned to the experimental condition, while comparison schools will continue with their typical curriculum. Data will be collected at baseline, post-course completion, and 3-month follow-up. The study protocol and tools for the study have been approved by the Non-Medical Research Ethics Board (initial REB# 116816; January 2021) at Western University and ethics approval for the full-scale implementation will be sought prior to recruitment and data collection. Additional approval from participating college/university ethics boards will be completed, if requested

### 2.2. Theoretical Underpinning

In light of the importance of self-efficacy in influencing ECEs’ teaching practices [10,24], the proposed research will apply Bandura’s Social Cognitive Theory [23] to develop an e-Learning course that can facilitate improved physical activity and sedentary behaviour-related knowledge and self-efficacy among pre-service ECEs. Bandura highlights the importance of verbal persuasion and vicarious experiences to promote knowledge acquisition and self-efficacy development [23]; as such, the e-Learning course will incorporate a number of practical scenarios that will serve as observational models from which pre-service ECEs can learn, along with verbal cues to help important messages resonate with them. Scenario-based knowledge checks will also be included to test pre-service ECEs’ practical application of learned course content; according to Bandura, receiving positive reinforcement following correct responses (i.e., mastery experiences) will foster task self-efficacy development and reproduction of the behaviour [30].

In addition to the Social Cognitive Theory, we will also adopt Mayer’s Cognitive Theory of Multimedia Learning which denotes that a multimedia presentation of material through various information processing channels (e.g., auditory and visual) can combine to produce logical mental constructs that facilitate knowledge acquisition [31]. Each information receiving channel has a finite capacity to process (new) information and knowledge [32]; however, Mayer notes that when a message is delivered through multiple channels, this reinforcement of the message can enhance learning. As such, the e-Learning course will optimally challenge these information processing channels by utilizing text, voiceover, videos, and animations. 

### 2.3. Implementation Framework

The CFIR is commonly used to promote the translation of research to practice; as such, the TEACH study will follow constructs (*n* = 39) within this framework to ensure the research project is appropriately designed and scalable if proven effective. The CFIR comprises five domains: 1. intervention characteristics (i.e., how the intervention is designed to fit the target organization; e.g., completing a needs assessment and collaborating with those in the early childhood education field); 2. outer setting (i.e., the external political/social context within which an organization resides; e.g., the network of colleges/universities within each province/territory that follow the same accreditation standards); 3. inner setting (i.e., characteristics of the organization undergoing the intervention; e.g., early childhood education programs have communicated their wish to receive additional education in physical activity and sedentary behaviour domains); 4. individual characteristics (i.e., characteristics of individuals within the target organization; e.g., pre-service ECEs’ own interest in pursuing this type of education); and, 5. implementation process (i.e., how the intervention is implemented to promote fidelity and acceptance; e.g., partnering with early childhood education program staff and instructors to champion the intervention). Following these implementation constructs throughout the research project will act as a marker for intervention scalability.

### 2.4. e-Learning Course Development

The e-Learning course has been designed to be an engaging method of education, differing from the traditional approach of adding narration to a PowerPoint presentation. This will be achieved by enhancing learner engagement with the content (by utilizing within-module knowledge checks and interactive educational graphics) and provide acceleration of expertise through the use of video-based scenarios (i.e., increasing vicarious experiences, an important construct for building self-efficacy; as per the Social Cognitive Theory; [23,33]). Given the train-the-trainer approach (i.e., using experts to train staff) is widely problematized in professional learning [34], specifically due to the inability to address the diversity and individual needs of the trainee and push their knowledge and growth, the online, self-directed platform of the TEACH study e-Learning course will allow colleges/universities to incorporate the course when and how they see fit (while also allowing students dive deeper into specific content areas of interest to foster their professional development and learning goals). This approach also ensures consistency in training across the country and promotes practical future application in the childcare environment [35]. The course will be produced by a highly skilled e-Learning design team (including instructional and graphic designers), and we will follow Clark and Mayer’s Evidence-Based Guidelines for e-Learning Design to ensure the mode of delivery supports optimal learning among pre-service ECEs [33]. 

Our team has developed specific e-Learning course content by way of a Delphi study, wherein international physical activity and sedentary behaviour experts (*n* = 26) proposed their top content areas to include in the course [36]. These content areas were pooled, and redistributed to the same experts, as well as 35 Canadian early childhood education experts, to be rated for their importance. From this generated content, the research team created associated learning objectives and module assessments (i.e., an online test to ensure the information was acquired) to complement accreditation standards for the early childhood education profession. The CFIR stresses the importance of tailoring interventions to the target population [37]; as such, we will solicit knowledge user input (from program instructors and pre-services ECEs) on module content and functionality throughout the e-Learning design phase. These collaborations will ensure the course content is contextually appropriate and the mode of delivery optimizes student learning. The e-Learning course will be hosted on a secure learning management system platform (Talent LMS), with a unique portal for each college/university, so pre-service ECEs can easily access it for completion in class or at home. To access the course, participants will simply create an account and login. Figure 1 outlines the proposed content of the 4-module e-Learning course.

### 2.5. Recruitment and Allocation

#### 2.5.1. Universities and Colleges with ECE Programs

To help ameliorate potential recruitment challenges and secure a diverse sample with representation from a number of Canadian provinces, we will draw on our established rapport with early childhood education post-secondary programs and will purposefully select colleges/universities (see sample size explanation below) and recruit their ECE programs to participate by emailing ECE program coordinators. Once 16 colleges agree to participate, allocation to the experimental and comparison conditions will occur. To safeguard the internal validity of the intervention, it is important to avoid randomly allocating individuals within each college to receive the training (or not), given the e-Learning course may be completed during pre-service ECEs’ class time and contamination may occur. As such, participating colleges/universities will act as the unit of randomization (i.e., clusters). Once consent has been obtained from the college/university representative (e.g., program coordinator/chair), the clusters will be stratified by province, college/university size, and college/university ECE program delivery mode (i.e., in-person, online, or blended learning). Blocked randomization will be performed to allocate clusters (1:1) using a computer-generated randomization tool (www.randomizer.org (accessed on 12 March 2022); the software will generate a number of 1 or 0) to either receive the training (experimental; “1”) or not (comparison; “0”).

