### 2.7. Sample Size

We used the ‘pwr’ package in R [38,39] to estimate the sample size for the analyses (Primary Objectives #1 and #2). These calculations suggest that we need 224 pre-service ECEs (112 per group) to detect a small-to-medium effect size (f^2^ = 0.053 or R^2^ = 0.05), with 2 groups (intervention and control) and 3 time-points (baseline, post-intervention, follow-up), 80% of the time, with an alpha of 0.025. As we will target college/university programs as units (clusters), the sample size will be adjusted to account for the clustering effect, where: D = design effect; *k* = anticipated cluster size (class size in this case); and *ρ* = the intra-cluster correlation coefficient, a measure of the degree of homogeneity among cluster subjects for a particular outcome investigated.
D = 1 + (*k* − 1) *ρ* = 1 + (164 − 1) (0.05) = 9.15

We estimate an average class size of 164 pre-service ECEs (based on our nationwide study of pre-service ECEs from 61 colleges; [19]). Based on a preliminary scan of early childhood education programs in Canada, programs across the country have comparatively similar curriculum; therefore, the intra-cluster correlation coefficient will be lower. For the purpose of estimating this sample size, we assumed a value of 0.05. Thus, the design effect is 9.15, and the sample size needs to be inflated. Finally, the sample will be further adjusted to account for loss to follow-up at 3 months (~30% attrition rate); therefore, the final targeted sample size will be 112 × 9.15/0.70 = 1464 ECE students per group.

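### Section 2.5.1 triggers allocation at 16 colleges, but the abstract and section 2.1 fix 18, and section 2.7 implies 9 per arm

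*Protocol article*

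**What the plan says.** Section 2.5.1 of the protocol article gives the operational rule: "Once 16 colleges agree to participate, allocation to the experimental and comparison conditions will occur". The same section makes the college or university the unit of randomisation, with stratified, blocked allocation at 1:1, so 16 colleges means 8 per arm. It refers the reader to the sample size explanation for the choice of colleges.

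Section 2.1 says that the clusters "will be randomly assigned to the experimental (*n* = 9) or comparison (*n* = 9) condition", which is 18 in total. The abstract gives the same 18, split 9 and 9.

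Section 2.7 starts from a calculation for individuals, stating that "we need 224 pre-service ECEs (112 per group) to detect a small-to-medium effect size". It multiplies by a design effect of 9.15 (164 students per college, intra-cluster correlation 0.05), allows for about 30% attrition, and concludes that "the final targeted sample size will be 112 × 9.15/0.70 = 1464 ECE students per group". It does not state how many colleges this needs.

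**The concern.** The number of randomised clusters is a core design quantity, and the article gives two values for it. The sentence with 16 is the one that staff would carry out. Followed as written, allocation takes place with two colleges fewer than the design describes. The article mentions no staged allocation and no reserve of two colleges that would bring the figures together.

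At stake is whether the trial is randomised at the size its own calculation calls for. A cluster count is hard to repair after allocation, so the conflict has to be settled beforehand.

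**Working it through.** **Inputs.** From section 2.7: 112 per group before adjustment, effect size f² = 0.053 (R² = 0.05), alpha 0.025, power 80%, k = 164 students per college, intra-cluster correlation ρ = 0.05, attrition 30%. From section 2.5.1: 16 colleges at 1:1, so 8 per arm. From the abstract and section 2.1: 9 per arm.

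**Step 1: reproduce the plan's figures.**
- Design effect: D = 1 + (164 − 1) × 0.05 = 9.15.
- Target: 112 × 9.15 / 0.70 = 1464.0 per group, an exact match.
- The starting figure of 224: section 2.7 names the software package and the effect size but not the numerator degrees of freedom, u. For an F test with noncentrality f² × N, the total N needed is 182 to 184 for u = 1, 221 to 223 for u = 2, and 249 to 250 for u = 3 (the range comes from f² = 0.053 or 0.05/0.95). For u = 2, 223 rounded up to equal groups is 224. So u = 2 fits best, but this is an inference.

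**Step 2: colleges implied by the target.** 1464 / 164 = 8.93, so 9 per arm and 18 in total.

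**Step 3: students supplied at 164 per college.**
- 9 per arm: 9 × 164 = 1476, which is 12 above the target.
- 8 per arm: 8 × 164 = 1312, which is 1464 − 1312 = 152 below it (152 / 1464 = 10.4%).

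**Step 4: effective sample size per arm, in section 2.7's order of steps** (students × 0.70 / D).
- 9 per arm: 1476 × 0.70 / 9.15 = 112.9.
- 8 per arm: 1312 × 0.70 / 9.15 = 100.4, against the required 112.

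**Step 5: power** (f² = 0.053, alpha 0.025, u = 2 assumed).
- 9 per arm, 225.8 effective in total: 81%.
- 8 per arm, 200.7 effective in total: 75%.

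**Step 6: how far the shortfall depends on the formula.**
- Attrition taken within clusters: 164 × 0.70 = 114.8 completers per college, D = 1 + 113.8 × 0.05 = 6.69, and 8 × 114.8 / 6.69 = 137 effective per arm. Power is about 89% (u = 2).
- ρ = 0.04 in the plan's order of steps: D = 1 + 163 × 0.04 = 7.52, and 1312 × 0.70 / 7.52 = 122 effective per arm.
- Both exceed 112 with 8 colleges per arm.

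**The case against.** The fair reply is that 16 is probably a stray number. Eighteen is stated twice and agrees with the sample size arithmetic, and the cost of the error is about 6 percentage points of power. That is a likely explanation, but the article does not give it, and the stray number stands in the sentence that governs randomisation.

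A reader might go further and infer that 8 per arm can never reach the requirement, however large the colleges are. Under section 2.7's formula the requirement per arm is 112 × [1 + 0.05(k − 1)] / 0.70 = 8k + 152, and 8 colleges supply 8k, so the gap is 152 at every k. This is a knife-edge result. It rests on ρ being exactly 0.05 and on attrition being applied after a design effect computed at full enrolment. With attrition taken within clusters, 8 per arm suffice from k = 64. The article therefore does not show that 16 colleges are underpowered under every reasonable method, or that larger colleges could not make up the difference.

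Two other readings go too far. The drop to 75% is not a stated property of the plan: with u = 1 the power at 8 per arm would be 84%, and with u = 3 it would be 69%, though neither reproduces 224. Nor is it the power of the linear mixed models in section 2.12. And one might fear that two colleges will be added after allocation, outside the stratified blocks, but the article says nothing of the kind.

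What stands is the contradiction itself, which needs no power argument, and the shortfall against the plan's own calculation.

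**Conclusion.** The point holds as an internal contradiction: 16 colleges in section 2.5.1 against 18 in the abstract and section 2.1, with section 2.7 implying 9 per arm at its own class size. Relative to section 2.7's calculation, following the 16-college rule leaves each arm 152 students (10%) short and gives about 75% power instead of the stated 80%.

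These sizes assume 164 enrolled students in every college, ρ = 0.05, 30% attrition applied after the design effect, and, for power only, an F test with 2 numerator degrees of freedom. They are not evidence that 16 clusters would be too few under other defensible calculations. The conflict should be reconciled before randomisation.

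**What to change.** Before allocation, do one of two things:

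- If 18 is intended, replace 16 with 18 in section 2.5.1. This costs one number.
- If 16 is intended, change the abstract and section 2.1 to 8 per arm, and restate in section 2.7 the sample size and the power that 16 clusters deliver. This costs a short recalculation.

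In either case, stating the number of colleges per arm and the numerator degrees of freedom in section 2.7 would let a reader check the figures. The first option restores consistency but leaves little margin. Nine colleges of 164 exceed the target by only 12 students, and by the plan's formula 9 per arm fall short once fewer than 152 students per college take part (9k is at least 8k + 152 only when k is at least 152). Section 2.5.2 makes participation in the surveys voluntary.

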#### 2.12.1. Primary Outcomes

Pre-service ECEs’ physical activity and sedentary behaviour-related self-efficacy and knowledge will be evaluated using two (self-efficacy, knowledge) linear mixed effects models wherein group and time are our primary fixed effects. Demographic variables will be used as predictors of pre-service ECEs’ self-efficacy, knowledge, and behavioural intention and perceived behavioural control in our analyses. Specifically, we will explore the extent to which province/territory predicts the dependent variables, and whether there is a significant effect of previous training, early childhood education program type, and mode of delivery. Based on previous research, the pre-service ECE population is largely female [19], so gender-based differences will not be explored. Finally, if baseline differences are observed, we will include student age, physical activity, and sedentary time as covariates in all models. 

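### Crossing province, size and delivery mode over 16 to 18 colleges leaves most strata too thin for blocked allocation to secure 9:9 or balance on those factors

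*Protocol article*

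**What the plan says.** Section 2.5.1 makes the college the unit of randomisation and states that "the clusters will be stratified by province, college/university size, and college/university ECE program delivery mode (i.e., in-person, online, or blended learning"). It continues: "Blocked randomization will be performed to allocate clusters (1:1) using a computer-generated randomization tool". The tool's output is described as "the software will generate a number of 1 or 0", with 1 meaning experimental and 0 comparison.

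The number of colleges is given in two ways. Section 2.5.1 says "Once 16 colleges agree to participate, allocation to the experimental and comparison conditions will occur". Section 2.1 says that colleges "will be randomly assigned to the experimental (*n* = 9) or comparison (*n* = 9) condition", and the Abstract agrees ("18; 9 experimental, 9 comparison").

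The number of provinces is left open: section 2.5.1 aims to "secure a diverse sample with representation from a number of Canadian provinces". Size classes and block size are not given.

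On the analysis side, section 2.12 allows control for observed baseline differences. Section 2.12.1 says "we will explore the extent to which province/territory predicts the dependent variables" and also lists previous training, program type and delivery mode. Section 2.12.2 names program type and province. College size is named in none of these three places.

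**The concern.** Stratified blocking balances arms only where a stratum holds enough colleges to fill a block. Three crossed factors, one of them province, spread over fewer than 20 units produce many strata with a single college. That college's arm is then decided without reference to any other college. The leftovers add up across strata, so the overall split can drift from 9:9 and the arms can differ on province, size or delivery mode.

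Two things are at stake. One is the planned 9 and 9, which matches the sample size calculation. The other, and the larger, is the balance on three factors that the sponsor singled out. With about 18 units, a chance difference in the type of college is hard to separate from the effect of the course unless the analysis adjusts for it.

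**Working it through.** **Where 9 per arm comes from (section 2.7).** The design effect is 1 + (164 − 1) × 0.05 = 9.15. The target is 112 × 9.15 / 0.70 = 1464 students per group. 1464 / 164 = 8.93, rounded up to 9 colleges per arm. The figure reproduces and is not in dispute. If allocation takes place with only 16 colleges, 9:9 is impossible; 8 per arm would give 8 × 164 = 1312 students.

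**Number of strata.** Delivery mode has three levels (section 2.5.1). Assuming two size classes, the strata number 2 × 2 × 3 = 12 with two provinces, 18 with three, 24 with four, 36 with six and 60 with ten. Three size classes and ten provinces give 90.

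**Main calculation.** Assume 18 colleges, each equally likely to fall in any of S strata, and permuted blocks of 2 within strata.

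- Probability that a given college is alone in its stratum: (1 − 1/S)^17.
- Expected share of strata with one college or none: (1 − 1/S)^18 + (18/S)(1 − 1/S)^17.
- A stratum with an even count contributes no imbalance; one with an odd count contributes +1 or −1 with equal probability. If J strata are odd, P(9:9 given J) = C(J, J/2) / 2^J. Averaging over the distribution of J gives the overall probability.
- Variance of the arm contrast for a split a:b, relative to 9:9: (1/a + 1/b) / (2/9).

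| Strata | Strata with 0 or 1 college | Colleges alone | P(9:9) | P(11:7 or worse) | P(12:6 or worse) | Mean variance increase |
|---|---|---|---|---|---|---|
| 12 | 55% | 23% | 0.33 | 0.20 | 0.03 | 1.9% |
| 18 | 74% | 38% | 0.28 | 0.28 | 0.07 | 2.7% |
| 24 | 83% | 49% | 0.26 | 0.32 | 0.10 | 3.2% |
| 36 | 91% | 62% | 0.23 | 0.37 | 0.14 | 4.0% |
| Coin toss | – | – | 0.185 | 0.48 | 0.24 | – |

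The coin-toss value for 9:9 is C(18,9) / 2^18 = 48620 / 262144 = 0.185.

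**Variance by split.** 10:8 gives 0.2250 / 0.2222 = 1.0125. 11:7 gives 0.2338 / 0.2222 = 1.052. 12:6 gives 0.2500 / 0.2222 = 1.125.

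**Sensitivity.** Simulations with 20,000 draws per scenario varied provinces (2 to 10), size classes (2 or 3), equal or unequal filling of strata, and blocks of 2 or 4. With 18 colleges, P(9:9) ran from 0.19 to 0.35 and P(11:7 or worse) from 0.18 to 0.46. In every scenario more than half of the strata held one college or none. Blocks of 4 did worse than blocks of 2, because they fill less often.

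**The case against.** Several counter-arguments have force.

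*The scheme is better than a coin toss.* A reader might infer that blocking does nothing here. The table does not support that: with 24 strata about half of the colleges share a stratum, and 11:7 or worse occurs with probability 0.32 against 0.48. Empty strata also count among those with one college or none, and they cause no imbalance. Nor does the 1 or 0 from the tool mean an unblocked draw; it is the arm label in a sentence that specifies blocking.

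*The precision loss is small.* Quoting only the 12.5% at 12:6 would mislead, because that split or worse has a probability of only 0.10 to 0.14 with 24 to 36 strata. Chance imbalance after random allocation is also not systematic bias; the standard error allows for it. Both points stand.

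*The article may be condensed.* Blocking down a list sorted by the three factors would fit the wording loosely and would give 9:9. Purposeful selection could also yield even strata. However, blocks within strata is the usual meaning of the description, and the stated reasons for selection are easier recruitment and diversity, not filling strata. The article names no device that secures overall balance.

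*The analysis may compensate.* Section 2.12 does allow control for observed baseline differences, so it is wrong to say that nothing is adjusted. The omission that stands is narrow: college size is named in no model. A reader might also conclude that entering province and delivery mode cuts the between-college degrees of freedom from 16 to 9. That needs six provinces (18 − 2 − 5 − 2 = 9) and a confirmatory model with those terms, whereas section 2.12.1 only proposes to explore province. The cost also differs for a group-by-time contrast, from which time-invariant main effects do not take degrees of freedom in the same way.

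**Conclusion.** The point holds as a design weakness that should be corrected. As described, the allocation does not secure 9:9: even the most favourable layout examined misses it about two times in three (1 − 0.35 = 0.65), and with four or more provinces P(9:9) is 0.19 to 0.28. The average effect of unequal arms on precision is minor. The more important consequence is that province, size and delivery mode are not reliably balanced, and that size is not mentioned in the analysis either.

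The figures rest on assumed numbers of provinces and size classes, assumed block sizes, blocking within fully crossed strata, and colleges falling into strata by chance. The direction of the result does not change over the range tried. The documents do not support describing the scheme as equivalent to a coin toss, as a source of bias, or as certain to lose seven degrees of freedom.

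**What to change.** 1. Reconcile the number of colleges: 16 in section 2.5.1 against 18 in the Abstract and section 2.1. Allocate only when the full number has agreed.
2. Replace stratified blocking with covariate-constrained randomisation. Colleges agree before allocation, so their characteristics are known. List the equal-arm allocations, keep those balanced on region (provinces grouped in advance into two or three groups), size and delivery mode, and draw one at random by script. This guarantees equal arms and improves balance on the sponsor's own factors. It is a good option, not the only one.
3. Adjust the primary models in section 2.12.1 for the same collapsed factors, including size. Keep the province-by-province exploration as a secondary analysis.

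The cost is a short script and a paragraph of text. Provinces must be grouped before allocation. The adjustment uses some between-college degrees of freedom: with three regions, two size classes and three modes, 18 − 2 = 16 becomes 18 − 2 − 2 − 1 − 2 = 11, and the critical t at two-sided 0.025 rises from 2.47 to 2.59.
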